**Fig. 1 Fig1:**
[figure not shown]
Consort flow chart for recruitment, allocation, enrolment, analysis and outcome measure

### The study setting

Astrid Lindgren Children’s Hospital, a tertiary hospital in Stockholm, Sweden.

### Participants

#### Recruitment of subjects

Infants at risk of CP or other neurodevelopmental disorders after neonatal events will be recruited from the regular check-ups that are carried out at 3 months of age within the standard clinical follow-up program at the Astrid Lindgren Children’s Hospital. Children will also be recruited via paediatric neurologists who are examining infants at risk of CP and other neurodevelopmental disorders who are referred to the hospital. These are infants that have typically been exposed to or present with perinatal risk factors such as preterm birth, hypoxia, infections, heart insufficiency, small for gestational age/growth restrictions, hypoxic ischemic encephalopathies (HIE), and morphological brain abnormalities. Infants that exhibit delayed psychomotor development or clinical signs of abnormal neurology will be considered eligible for study participation.

Parents of eligible infants will be informed about the study only after discussions between the medical hospital team and the study coordinator regarding the high-risk status of the child. Families will be given a site-specific information sheet regarding the study, and they will have the opportunity to speak with investigators before consenting to participation in the study. Children of parents who do not wish to participate in the study will continue to receive usual care in the hospital and later on at the habilitation services.

*Inclusion criteria* will be based on a combination of assessments, including the Alberta Motor Infants Scale (using 2SD as the cut-off) and the Hammersmith Infant Neurological Examination (HINE) together with other findings from clinical neurological examinations. Magnetic resonance imaging (MRI) will be used if available to support the risk of development of CP, but only MRI examinations conducted as part of the clinical care will be used. If a child is found to be possibly eligible, the neurological signs indicating risk of CP must also be present at a second examination carried out approximately 3 weeks after the initial assessment before the child is invited to participate in the study. The inclusion age will vary between 4 and 8 months depending on the clarity of signs and time of referral to the hospital. A diagnosis of CP or not will be made by an experienced child neurologist at 2 years of age based on the SCPE criteria (www.scpenetwork.eu), and other neurodevelopmental diagnoses will be based on their specific criteria.

*Exclusion criteria* will be unstable health, uncontrolled epilepsy, progressive disorders, or diagnosis with a specific syndrome. A further exclusion criterion will be children for whom neither parent is fluent in Swedish or English. Satisfactory skills in either language are required for participation in data collection and the coaching and education program.

#### Sample size

The study sample size has been estimated from the pilot project of Morgan et al [19]. Thirty participants (15 per group) has been estimated using motor composite scores of the Peabody Developmental Motor Scale (PDMS-2) with an alpha value of 5 % and power of 80 %, a minimal clinically important difference of 10 %, and a 20 % drop out rate. The Small Step Program has not previously been used, but it has similarities to the method of Morgan et al [19]. However, the design of the Small Step Program requires sub-analysis of growth curves. This requires a higher N, and the planned study sample size is therefore increased to 48 children (24 per group). Interim analysis will be done continuously to control for sample size.

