## Statistical methods

Descriptive data for each outcome measure (primary and secondary) will be summarized and presented for both treatment groups (Small Step or treatment as usual). Changes over time and developmental trajectories will be investigated in both groups for each outcome measure with the use of mixed models, repeated-measures ANOVA, or corresponding non-parametric options depending on the data level and the distribution of data and in accordance with guidelines for RCTs. Post hoc analysis with correction for multiple comparisons will be applied when suitable. Group comparisons on all outcome measures will be made at 14 weeks and approximately 35 weeks after the start of the intervention and when the participants are 2 years old. All analyses will be conducted using IBM SPSS Statistics 22, and a significance level of *p* < 0.05 will be used.

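### Continuous interim analysis steers the sample size while the test level stays at 0.05; if those looks compare the arms, the 5% error rate is not kept

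*Protocol article*

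**What the plan says.** The Sample size section of the protocol article derives 30 children, 15 per group, from an outside pilot, "with an alpha value of 5 % and power of 80" per cent, "a minimal clinically important difference of 10" per cent and "a 20 % drop out rate". It then raises the planned number to 48, 24 per group, because the sub-analysis of growth curves needs more children. The section closes with: "Interim analysis will be done continuously to control for sample size".

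The Statistical methods section says that "a significance level of *p* < 0.05 will be used", for all analyses. It offers correction for multiple comparisons only for post hoc analysis, where suitable, and does not link this to interim looks.

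**The concern.** The sentence fixes two things: how often interim analysis happens (continuously) and what it is for (to govern the sample size). Set beside an unadjusted 0.05, this allows the arms to be compared repeatedly, with recruitment ended or prolonged according to the result and the final p-value read as if there had been one test. Each extra look is another chance to cross 0.05 by luck, so a reported p-value just under 0.05 would be weaker evidence than it appears. The section also contains two sample sizes, 30 as calculated and 48 as planned, so there is an obvious intermediate point at which a favourable trend could end recruitment.

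**Working it through.** **1. The plan's own figure.** For two means, n per arm = 2 (z₀.₉₇₅ + z₀.₈₀)² SD² / δ², divided by (1 − 0.20) for dropout. No SD is given, and it is unclear whether the 10% difference is relative or in scale points, so 30 cannot be checked directly. Assume a two-sided test and δ = 10 points:

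- SD 8.5: 2 × (1.960 + 0.842)² × 8.5² / 10² = 11.3, so 12; 12 / 0.80 = 15 per arm, 30 in total.
- SD 8 gives 28 in total, SD 10 gives 40, SD 15 gives 90.

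The stated 30 is therefore attainable with an SD of about 8.5 points. The missing SD does not affect what follows, because under the null the t-test does not depend on it.

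**2. Inputs for the error rate.** Planned size is 24 per arm; after 20% dropout, 24 × 0.80 = 19.2, taken as 19 evaluable. The nominal level is 0.05, assumed two-sided. The number and timing of looks are not stated, so a range is shown.

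**3. Method.** In each of 200,000 trials simulated with no true difference, at a look with n per arm, T = (difference in means) / (s √(2/n)). The trial counts as a false positive if |T| exceeds the 97.5% point of t with 2n − 2 degrees of freedom at any look. Near 20% the simulation standard error is √(0.2 × 0.8 / 200,000) = 0.0009, about 0.1 percentage point.

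| Looks, each at p < 0.05 | Type I error |
|---|---|
| 24 per arm, final analysis only | 5.0% |
| 15 and 24 per arm (the two sizes in the article) | 7.9% |
| 2 equally spaced to 24 | 8.3% |
| 3 equally spaced to 24 | 11.0% |
| 4 equally spaced to 24 | 12.9% |
| After every pair, from 12 to 24 per arm | 13.4% |
| After every pair, from 8 to 24 per arm | 16.9% |
| After every pair, from 5 to 24 per arm | 20.3% |
| After every pair, from 12 to 19 per arm | 11.0% |
| After every pair, from 5 to 19 per arm | 18.3% |
| 24, extended to 36 per arm if not significant | 7.6% |
| 24, 30, 36, 42 and 48 per arm | 11.2% |

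**4. The benign alternative.** The sample size was reset once from the variance of all children together at 12 per arm, without arm labels, for an assumed standardised effect of 0.83. Type I error was 5.0% when the size could move between 24 and 48 per arm, and 5.0% when it could move between 15 and 24.

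**5. What error control would require.** With 24 per arm, the constant level per look that holds the overall rate at 5% is about 0.029 for two looks, 0.022 for three, 0.017 for four, and 0.009 for a look after every pair from 5 per arm. The article applies 0.05 throughout.

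**The case against.** The sentence is ambiguous. It mentions no between-arm test, no stopping for efficacy and no extension. It follows assumptions borrowed from a pilot of a similar but different programme, so following variance or dropout is a plausible meaning, and step 4 shows that this does no harm. Schedules and boundaries are also commonly left to a full protocol or analysis plan, which is not shown. The 20% figure needs a formal test after every pair from 5 per arm. Because outcomes mature about 35 weeks after the start, fewer looks may be feasible than the wording suggests.

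Much of this stands. It makes the inflation conditional and its size a range. It does not clear the text. The point is not that boundary details are absent, but that the article states continuous looks that govern the sample size together with an unadjusted 0.05. An unseen plan could repair that only by narrowing the published sentence.

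A reader might also infer that the investigators who recruit and allocate would see accumulating results. The documents do not say so. The Randomisation section has the principal investigator holding the list, and the Study protocol section describes team reviews of the project process, but neither says who runs interim analyses or who sees results by arm. Nor can it be assumed that interim trends would bias assessment. The Blinding section has video-based measures scored blind and keeps data collectors out of treatment, although data collectors do know the allocation and the article does not say whether the primary scale is scored from video.

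**Conclusion.** The concern holds in conditional form. The stated interim rule and the stated significance level do not together guarantee a 5% error rate, and nothing in the article confines the looks to a form that would. If the looks compare the arms and can stop, extend or support a claim, the two-sided type I error is about 8% with two looks, 11 to 13% with three or four, and about 20% with a look after every pair from 5 per arm at 24 per arm (11 to 18% with 19 evaluable per arm, depending on when the looks start). These figures assume a two-sided t-test at 0.05 at each look; the true number of looks is unknown.

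The stronger reading, that the trial's false-positive rate is definitely inflated, is not supported, since monitoring without arm labels would leave it near 5%.

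**What to change.** Either of two changes is enough:

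- delete the interim sentence and keep the total fixed at 48; or
- replace it with a statement that interim monitoring uses pooled data only (recruitment, dropout, overall variance), with no between-arm comparison.

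A formal recalculation of the sample size from the pooled SD is not proposed: the article gives no planning SD to compare it with, and 48 was chosen for the growth-curve sub-analysis.

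If a between-arm look is wanted, limit it to one, fix its timing in advance, use an O'Brien-Fleming type alpha-spending boundary, and lower the final significance level in the Statistical methods section to match.

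The cost of the first two options is wording only, plus giving up informal looks at arm differences. The third also costs a little power at the same sample size. If pooled monitoring was meant all along, the change only makes that explicit.

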#### Randomisation

The baseline assessments of the children will occur prior to randomization after informed consent is collected. The randomisation is based on a prepared random assignment number list kept by the principal investigator (PI) in a locked room. The children will be allocated to group by block randomisation*.* Stratification will be used to control for gestational age (preterm <37 weeks and term >37 weeks). The infant will be assigned to the next position and added to the list by the PI. If an infant is later excluded for any reason, the infant’s position in the randomisation list will not be replaced by any new infants. Children in the Small Step Program will be further randomised to start with either the mobility or hand use focus.

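### The principal investigator both keeps the randomisation list and enters each infant on it, so the described procedure does not ensure that allocation is concealed from a person who helps run the trial

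*Protocol article*

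**What the plan says.** The Randomisation section of the protocol article gives the mechanism in a few sentences.

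- **Custody:** the basis is "a prepared random assignment number list kept by the principal investigator (PI) in a locked room".
- **Assignment:** "The infant will be assigned to the next position and added to the list by the PI".
- **Type:** "The children will be allocated to group by block randomisation". No block size is stated.
- **Strata:** gestational age in two classes, "preterm <37 weeks and term >37 weeks".
- **Order of events:** "The baseline assessments of the children will occur prior to randomization after informed consent is collected".
- **Exclusions:** the position of an infant excluded later is not given to another infant.
- **Second randomisation:** infants in the Small Step arm are randomised again to start with mobility or hand use. No separate custody arrangement is described for it.

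Three other sections bear on the point. Study protocol lists the PI among three people who handle project organisation. Recruitment of subjects sets out how infants become eligible and when they enter. Blinding says that families and the therapists who collect data know the group, while those who score video-based measures do not.

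**The concern.** Concealment means that nobody who can affect entry knows the next assignment until the infant is irrevocably in the trial. Here custody of the sequence and its execution lie with the same person, who is also a trial leader. The stated safeguard, a locked room, works against everyone except that person.

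If the next slot is known, the decision to approach a family now, later or not at all can drift with it, without any intention to cheat. The arms may then differ in prognosis at entry. Adjustment for measured baseline variables removes only part of such a difference, and it cannot be reliably repaired afterwards. With 48 infants, and with families and data collectors aware of group, concealed allocation is one of the few protections open to this trial.

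**Working it through.** The plan states no figure on this point, so there is none to reproduce. The check sets the sections side by side.

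**1. Does the procedure conceal the sequence from its keeper?** The list is prepared in advance, the PI keeps it, and the PI writes each infant on it. The article mentions no sealed envelopes, independent holder or central service. As described, the PI can know the next entry in each stratum before an infant is entered.

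**2. Is the keeper remote from the conduct of the trial?** No. Study protocol puts the PI among the three organisers.

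**3. Is there discretion before entry on which foreknowledge could act?** Recruitment of subjects shows some:
- Eligibility uses two scales, one with a 2 SD cut-off, "together with other findings from clinical neurological examinations". It is partly a matter of judgement.
- Signs must still be present at a second examination about 3 weeks later. This tightens eligibility, but it also lengthens the time before entry.
- Entry may fall between 4 and 8 months (the abstract says 3 to 8), according to how clear the signs are and when the child is referred.
- Families may talk with investigators before they consent.

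**4. What do the stated safeguards cover?** Consent and baseline before randomisation keep the baseline measurements free of the allocation. Not replacing excluded infants stops a slot being reused. Neither acts on the earlier decision of whom to invite and when.

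**5. How much does the keeper know compared with others?** Someone who can read the list knows 100% of coming assignments. Someone who knows neither the list nor past assignments guesses correctly 50% of the time. In between is a person who sees past assignments and knows a fixed block size. With *a* and *c* slots of each arm left in a block, the expected number of correct guesses is

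f(a,c) = max(a,c)/(a+c) + [a/(a+c)]·f(a−1,c) + [c/(a+c)]·f(a,c−1), with f(0,0) = 0.

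For blocks of 2, f(1,1) = 0.5 + 1 = 1.5. For blocks of 4, f(2,1) = 2/3 + (2/3)(1.5) + (1/3)(2) = 2.333, so f(2,2) = 0.5 + 2.333 = 2.833.

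| Block size (assumed) | Correct per block | Share | Of 48 |
|---|---|---|---|
| 2 | 1.50 | 75% | 36 |
| 4 | 2.83 | 71% | 34 |
| 6 | 4.10 | 68% | 33 |
| 8 | 5.33 | 67% | 32 |

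The article gives no block size, so these rows are illustration only. They show why block sizes should stay undisclosed once the list is moved.

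**6. Can the bias be sized?** Not from the document. It would need the share of entries steered, the direction, how well clinical impression predicts the outcome, and whether a passed-over infant is lost or enters later. None of these is given. Trial simulations were run at 24 per arm with no true effect and assumed blocks of 4. Infants in the outer quarters of prognosis were steered 25% or 50% of the time. Varying that rate, the prognosis–outcome correlation (0.5 or 1) and the fate of passed-over infants moved the difference between arms from about 0.1 SD to about 0.6 SD. Its sign depends only on which way the steering is assumed to go. A range that wide reflects the assumptions and is no estimate for this trial.

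**7. Stratum boundary.** The two classes are below 37 and above 37 weeks. Read literally, an infant born at exactly 37 weeks belongs to neither.

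**The case against.** Four points on the other side are fair.

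- **The list may be sealed in practice.** The article does not say that entries are visible, and a condensed article may leave out envelopes. A reader might infer that the list is open and allocation plainly unconcealed. The text does not support that. What stands is that the article describes its mechanism, and as described that mechanism does not ensure concealment from the keeper. If a device exists, one sentence settles the matter.
- **The PI is not named as recruiter.** Discussion of risk status before parents are approached lies with the clinical team and a study coordinator. A reader might infer that the PI picks the infants, but no section says so. What stands is that an organiser who may be among the investigators speaking with families is close enough to influence invitation or timing.
- **Consent and baseline already come first.** This is true and useful, but it does not reach the invitation stage.
- **Primary outcome scoring.** A reader might infer that the Peabody scale is scored unblinded, which would make the problem worse. The Blinding and outcome sections do not say whether it is scored live or from video, so the point here does not rely on it.

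The 37-week gap is a separate drafting slip that affects only infants at the boundary. That the PI would choose their list is conjecture.

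**Conclusion.** The concern holds in a limited form. The same trial leader keeps the sequence and makes the assignments, and the stated safeguard does not act on that person. Concealment is therefore not assured, and selection bias is possible. The document does not show that allocation was foreseen, that entry was steered, or in which direction any bias would run, and no numerical size should be attached.

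The conclusion rests on reading the Randomisation section as a description of the actual procedure, with no unreported concealment device. If there is one, what remains is a reporting gap and the 37-week boundary.

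**What to change.** 1. Have the sequences for both the group and the hand-use/mobility randomisation held by an existing institute staff member with no role in eligibility, consent, treatment or assessment.
2. Release each allocation only after eligibility, consent and completed baseline are logged for an identified infant. Opening the next sequentially numbered opaque sealed envelope at that point is an acceptable alternative.
3. Keep block sizes undisclosed to the investigators.
4. If such a device is already in use, say so in the text.
5. Minor: close the stratum boundary so that infants born at exactly 37 weeks fall in one class, for example below 37 versus 37 weeks or more.

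The cost is a short administrative step at each randomisation and a few sentences of text. Sample size, visits and assessments do not change.

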### Primary and secondary objectives

The primary objective of this trial is to evaluate the effects of the newly developed Small Step Program on general development in children at risk for developing CP or other neurodevelopmental disorders. The main hypothesis of the study is that the Small Step Program is more effective than treatment as usual when children are evaluated at the age of 2 years. The rapid brain development and plasticity during the first year of life is utilized as a possible therapeutic window for intensive training. The design of the program, with three different foci during separate time periods, was designed in relation to the second hypothesis. We assume that children will have a more rapid development within the specific focus of each time period compared to the development rate within the other two foci that are not being trained at that particular time: i.e. you learn what you practice. The third hypothesis is that children’s ability to develop will be influenced by the specific characteristics of any underlying brain pathology.

The secondary objective is to evaluate the effect of the Small Step Program on parents’ ability to cope with the stress and anxiety related to the traumatic experience of parenting a child at risk of developing CP. The hypothesis is that parents in the Small Step Program will be less stressed and can better cope with their child’s situation than parents of children receiving usual care. Thus, the tools provided within the Small Step Program like coaching, supervision, education, and feedback on how to stimulate task performance and communication will make parents more able to cope with the child’s delayed development.

The study will be a randomised, controlled, prospective, parallel-group trial based on the Consolidated Standards of Reporting Trials (CONSORT) statement regarding the randomised trial of non-pharmacological treatments. Children will be randomised to one of two arms – the Small Step Program or treatment as usual. The children in the Small Step Program will be further randomised to start with either hand-use or mobility (Fig. 1). The rationale for the second randomisation is based on the *second* hypothesis.

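### The article foresees exclusions after allocation without saying those infants stay in follow-up and analysis, and it leaves open a repeated-measures ANOVA that drops children with a missed visit.

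*Protocol article*

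**What the plan says.** The Randomisation section describes allocation from a prepared list held by the principal investigator: "The infant will be assigned to the next position and added to the list by the PI". The text then turns to later exclusion: "If an infant is later excluded for any reason", the infant's "position in the randomisation list will not be replaced by any new infants". No reason is ruled out, and nothing is said about whether such an infant still attends assessments or is included in the analysis.

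The exclusion criteria, given with the recruitment rules, include "unstable health, uncontrolled epilepsy, progressive disorders, or diagnosis with a specific syndrome".

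The Statistical methods section says that change over time and developmental trajectories will be studied in both groups "with the use of mixed models, repeated-measures ANOVA, or corresponding non-parametric options depending on the data level and the distribution of data", and adds "in accordance with guidelines for RCTs". Group comparisons are planned at 14 weeks, about 35 weeks and 2 years of age, in SPSS 22. The objectives section describes the trial as "based on the Consolidated Standards of Reporting Trials (CONSORT) statement regarding the randomised trial of non-pharmacological treatments". The text contains no explicit commitment to analyse every infant in the allocated group.

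**The concern.** Randomisation makes the two groups comparable only while the groups analysed are the groups allocated. Two features of the text leave room to depart from that. First, an infant can be excluded after allocation, and the text does not say that the infant's data are still collected and used. Second, one of the permitted analyses keeps only children with a complete set of visits, and the stated basis for choosing among the methods (data level and distribution) does not include missing data.

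If the infants lost in either way differ in prognosis from those who remain, and the losses differ between arms, the estimated effect is biased. Some circumstances make this more than a formality. Families and the therapists who collect data know the allocation. The arms differ in contact: weekly coaching and extra assessments at 7, 21 and 28 weeks in the programme arm, against less frequent visits in usual care. With 24 infants per arm, a few selective losses can move a mean noticeably.

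**Working it through.** **The plan's own figures.** The sample-size section gives 15 per group with 20% drop-out, so 15 × 0.8 = 12 evaluable per group, and then raises the plan to 24 per group. No SD is given, so the figure of 15 cannot be reproduced independently. The point does not depend on it. The 20% is a drop-out assumption for that calculation. Applied to the planned size it leaves 48 × 0.8 = 38.4 infants, about 19 per arm.

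**Effect of losing infants from one arm.** Input from the article: 24 per arm. Assumption: k infants are lost from one arm, none from the other, and the lost infants average 1 SD below those who remain. The full-arm mean then lies k/24 SD below the mean of the remaining infants, so the observed mean rises by k/24. The standard error of the difference between arms, in SD units, is √(1/24 + 1/(24 − k)).

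| k lost | Shift k/24 (SD) | Standard error (SD) | Shift / standard error |
|---|---|---|---|
| 2 | 0.083 | √(1/24 + 1/22) = 0.295 | 0.28 |
| 3 | 0.125 | √(1/24 + 1/21) = 0.299 | 0.42 |
| 5 | 0.208 | √(1/24 + 1/19) = 0.307 | 0.68 |

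The form k/(24 − k), which gives 5/19 = 0.26 SD for five infants, applies only if the lost infants average 1 SD below the whole arm. That is a different and more extreme assumption.

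**Effect on the test.** In 100,000 simulated trials with 24 per arm, normal outcomes, no true effect and a two-sided t-test at 5%, infants were removed from one arm only:

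- Five removed, with a correlation of 0.3 to 0.5 between exclusion and outcome: bias 0.10 to 0.17 SD, type I error 6.4% to 8.9%.
- Two removed, same correlations: bias 0.05 to 0.08 SD, type I error 5.4% to 5.9%.
- Worst case, the five lowest scorers removed: bias 0.35 SD, type I error 24%.

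The correlations and counts are assumptions; the documents give none.

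**Complete cases under repeated-measures ANOVA.** Both groups have three post-baseline visits. If each is missed independently with probability m (an assumption), the expected number of complete cases is 48 × (1 − m)³:

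- m = 2%: 45.2
- m = 5%: 41.2
- m = 10%: 35.0
- m = 20%: 24.6

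A mixed model would use the attended visits of the children that this analysis discards.

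**The case against.** The strongest reply is that the exclusion sentence is a rule about list positions. It is conditional, and by forbidding refilling it protects the allocation sequence. A reader might infer that it permits exclusion at will, or that excluded infants leave the analysis. It says neither, and this part of the reply stands. What remains is that exclusion after allocation is foreseen, without limit on the reason, and the infant's later status is left open.

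Second, the exclusion criteria are entry criteria. A reader might infer that an infant who later develops epilepsy or receives a syndrome diagnosis would be removed. Nothing says the criteria are re-applied after allocation.

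Third, a reader might infer that bias would favour the programme, because contact there is more frequent. The documents do not support a direction. Weekly contact is coaching, not diagnostic examination; all children follow the hospital programme; and unblinded control families might leave just as readily.

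Fourth, the article nowhere prescribes a complete-case analysis. Mixed models are listed first, the listed methods are attached to change over time, the sentence on group comparisons names no method, and the abstract speaks of general linear models. This shows that repeated-measures ANOVA is not fixed as the between-group analysis. It does not close the option: the section names no other method for the comparison, and repeated-measures ANOVA in its standard SPSS form is itself a general linear model.

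Fifth, analysis sets and missing-data rules commonly sit in an analysis plan or full protocol, neither of which is shown. Their absence alone would be no finding. The point rests instead on two things the article does state: open-ended exclusion after allocation, and a named method that discards incomplete records. The references to CONSORT and to RCT guidelines point towards an as-randomised analysis but do not fix one.

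**Conclusion.** The point holds in limited form. The article foresees exclusion of allocated infants without saying they remain in follow-up and analysis, and it leaves open a method whose standard form drops children with a missed visit. The comparison need not be of the groups as randomised; the documents do not show that it will not be.

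The size depends on assumptions. One-sided loss of 2, 3 or 5 of 24 infants averaging 1 SD below the rest shifts that arm's mean by about 0.08, 0.13 or 0.21 SD, which is 0.28 to 0.68 of a standard error. Similar losses in both arms would largely cancel in the difference, and losses unrelated to outcome would cost precision without bias. The 20% drop-out figure should not be read as an allowance for exclusions. The change is worth making because it costs little and the arms are small.

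**What to change.** Add to the Randomisation or Statistical methods section that every randomised infant is invited to all planned assessments and analysed in the allocated arm, including infants later found to meet an exclusion criterion and those whose family leaves the programme. This concerns data collection and analysis only and changes no clinical care.

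For outcomes suited to it, name the mixed model on all available visits as the main between-group analysis, in place of complete-case repeated-measures ANOVA. The mixed model still assumes that missingness is explained by the observed data, so continued follow-up is the more important half of the change. Report exclusions and losses by arm, with reasons and timing.

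The cost is wording, slightly more effort to bring families to visits that are already scheduled, and a little more analysis work. No visit, measure or participant is added.
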